**Interventions**			
Standard decolonization + clindamycin	X	X	X
Standard decolonization + placebo	X	X	X

^*^If MRSA positive at *T*_1 month_, the participant leaves the trial and will not be sampled in the trial at *T*_6 month_

If MRSA-negative at 1 month, no unblinding will take place at this point. The participant will have new control swabs taken at the GP 6 to 8 months after completing the treatment, as generally recommended. If MRSA-negative at 6–8 months after treatment, the participant is declared MRSA-free according to the national MRSA guidelines.

### Sample size {14}

The anticipation is a 30% increased decolonization rate based on non-published data described in the background and rationale section in the group receiving standard treatment plus clindamycin compared with the group treated with standard treatment and placebo.

Power calculation shows that we will need 31 patients in each group. It is our goal to include 40 patients in each group, as we expect that 9 patients in each group will either drop out or be non-compliant to the treatment.

### Compliance and adherence {11c}

Compliance is defined by having consumed more than 80% of the oral capsules. We expect patients in both groups to be equally compliant. In the diary handed out with the decolonization package, study subjects are instructed to record how many capsules, if any, are left after the treatment to monitor compliance. The diary should be returned as quickly as possible to the investigator, with any leftover capsules in a pre-stamped envelope. The number of returned capsules will be reported in the eCFR. If participant control swab results are not registered approx. 30 days after completing the treatment, or diary and left-over capsules are not returned, friendly reminders are sent to the participant by email {18b}.

### Eligibility criteria {10}

Inclusion criteria:Age ≥ 18 yearsMRSA carriage in the throat after the first topical decolonization treatment (regardless of previous swab results)Has completed one standard topical decolonization treatment

Exclusion criteria:Pregnant or lactating womanSexually active women of reproductive age that do not use approved contraceptivesCannot read or speak DanishSkin infection or other active infectionsActivity in skin diseases such as eczema or psoriasisMRSA isolate resistant to clindamycin (defined by inhibition zone size < 22 mm using EUCAST disk diffusion methodology) or resistant to mupirocinAllergy to clindamycin, chlorhexidine, or mupirocinTaking medications that interact with clindamycin according to the medicine information leafletMRSA-active antibiotic treatment within 7 days before inclusion in the study or during the study periodFollowed by specialist due to liver diseaseSevere overweight (body mass index (BMI) > 35) or weight < 50 kgIndwelling percutaneous permanent devices such as intravenous catheters or urinary tract cathetersDaily contact with pigs or minks (decolonization is generally not offered, according to the National Board of Health)Nursing home resident or health care worker (alternative swab regime is recommended)Not being capable of completing another treatment successfullyMRSA-positive household members younger than 2 years (MRSA-positive children below 2 years of age and their household members are generally not offered decolonization treatment according to the National Board of Health)MRSA-positive household members, where it is determined that further decolonization attempts are not indicated

### Modifications {11b}

Participants will be informed that participation is voluntary and that they have the right to leave the study at any given time, without providing a reason, and with no loss of benefits concerning treatment outside the study. If a participant withdraws, we will be able to use the results that we have at the given time of the withdrawal, as mentioned in the handout information. The investigator has the right to terminate participation if considered in the best interest of a given participant.

### Concomitant care {11d}

Hospitalization and other interventions interfering with the compliance of the trial will inevitably result in terminated trial participation.

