### MRSA patients

In the Capital Region of Denmark, the number of new MRSA-positive patients ≥ 18 years was 855 in 2018 with an estimated MRSA prevalence of < 0.5% [14, 15]. In around 60% of cases, MRSA is first found in a sample from an infection (mainly skin and soft tissue infections), and approximately 75% of these patients are MRSA carriers following the infection. Therefore, we expect to encounter approximately 700 newly diagnosed MRSA carriers per year of which around 66% are throat carriers in their first screening sample (462 patients). Based on retrospective data, around 40% become MRSA-free after the first decolonization treatment, which means that approximately 277 of the throat carriers ≥ 18 years old are still MRSA-positive after the first treatment. We expect that 40% of these patients have one or more exclusion criteria and therefore end up with approximately 330 patients that fulfill the inclusion criteria within the study period. As a part of our working routine, we automatically obtain information about all MRSA culture-positive samples in the lab on daily basis.

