### After the treatment

Thirty to 60 days after the end of treatment, the participants will routinely have MRSA control swabs taken by their general practitioner (GP) according to the national MRSA guidelines. Control swabs and the results of these are handled routinely. In laboratory settings, Eswabs (Copan) are inoculated in an enrichment broth containing 2.5% NaCl, 3.5 mg/L cefoxitin, and 20 mg/L aztreonam for overnight incubation at 35 °C. From the broth, 10 μL is spread on a 5% blood agar and an MRSA chrome agar (Biomérieux). Susceptibility testing is performed by disk diffusion using EUCAST breakpoints. MRSA-positive isolates are confirmed by an in-house PCR [16].

If the participant is MRSA-positive 1 month after the treatment, the participant will leave the trial, and the randomization will be unblinded in order to plan the most optimal treatment outside the trial, without revealing the given treatment to the investigator, leaving the investigator blinded until the end of the trial, approximately September 2025 (currently planned), when the final swab results from the last included participant have been analyzed (Table 1) {13}.

**Table 1 Tab1:** Schedule of enrollment, interventions, and assessments

	Enrolment and allocation of treatment	Post-treatment control swab	Post-treatment control swab*
**Timepoint/assessments**	***T***_**0**_	***T***_**1 month**_	***T***_**6 month**_
Enrollment	X		
Eligibility screen	X		
Informed consent	X		

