### Statistics {20a/b/c}

Continuous data are expressed as median and range. Power calculations are based on an expected proportion of 20.3% in the control group and a minimum relevant difference of 30% points resulting in an expected 50.3% in the intervention group. Power is set at 80 and significance level at 0.05%. Since only superiority is of interest, a one-tailed *p*-value will be used. The statistical software “R” [17] was used for power calculation. The analysis will be performed using Fisher’s exact test or chi-squared test depending on sample size. Statistical calculations will be performed using IBM SPSS Statistics, version 25, IBM Corporation, and other(s) 1989, 2018. We intend to include every study participant randomized in the primary analysis, only omitting excluded participants, where no data is available after randomization or in case of lack of compliance. Missing data will be excluded from the analysis. No subgroup or interim {21b} analysis is planned.

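### Rules that remove participants for events after randomization do not separate stopping study treatment from stopping outcome follow-up, so 1-month results would probably be lost for reasons plausibly linked to arm and outcome

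*Protocol article*

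**What the plan says.** Five parts of the protocol article bear on this point.

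- **Concomitant care {11d}:** "Hospitalization and other interventions interfering with the compliance of the trial will inevitably result in terminated trial participation". No exception is given, and nothing is said about outcome data afterwards.
- **Eligibility criteria {10}:** one exclusion criterion, on drugs active against MRSA, reads in part "antibiotic treatment within 7 days before inclusion in the study or during the study". Its first half can be checked at enrolment; its second half can only happen after randomization.
- **Statistics {20a/b/c}:** the primary analysis is intended to include every randomized participant, "only omitting excluded participants, where no data is available after randomization or in case of lack of compliance". In addition, "Missing data will be excluded from the analysis".
- **Modifications {11b}:** "If a participant withdraws, we will be able to use the results that we have at the given time of the withdrawal". This concerns participants who withdraw.
- **After the treatment:** of the control visit, set at 30–60 days once the course is over, the section says: "the participants will routinely have MRSA control swabs taken by their general practitioner (GP) according to the national MRSA guidelines". The 1-month outcome swab is thus part of ordinary care.

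**The concern.** Two rules act on events after randomization: admission or an interfering intervention ends participation, and a later MRSA-active antibiotic is listed as an exclusion. The protocol itself gives reasons to think that such events are not random with respect to arm or result.

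- **Arm.** The section on serious adverse events lists pseudomembranous colitis, vomiting, diarrhoea and hypersensitivity among the known clindamycin reactions. Some of these could lead to admission or to an interfering treatment.
- **Outcome.** The background says that MRSA carriers are at risk of infection. A participant who has not been cleared is therefore plausibly more likely to need MRSA-active antibiotics or admission, and that participant is a failure on the primary outcome.

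If such participants drop out of the analysis, the arms compared are no longer the arms randomized. Losing clindamycin failures flatters clindamycin; losing placebo failures works against it.

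This differs from the omission for non-compliance. Someone who took all the capsules and was then given antibiotics for an infection before the swab is not non-compliant under the 80% capsule definition, yet falls under the exclusion wording.

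**Working it through.** **1. How a result would be lost.** Capsules are taken for 10 days (Interventions {11a}) and the swab follows 30 to 60 days after the end of treatment, so 40 to 70 days pass between the first capsule and the primary outcome. Consider a participant removed in that interval:

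- Participation has ended, and the protocol does not say that the swab will still be collected for the trial.
- If no swab result is recorded, the complete-case rule drops the participant. If the participant counts as excluded and has no data after randomization, or is non-compliant, the omission rule does so as well.
- A participant removed after the 1-month swab keeps that primary result.

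Loss before the swab is therefore the probable consequence of reading the rules together; it is not a stated one.

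**2. The plan's own figure.** Inputs from Statistics {20a/b/c}: p1 = 0.203, p2 = 0.503, 80% power, one-sided test. The significance level is printed as 0.05%; 0.05 is used here because only that value reproduces the stated size. The mean rate is 0.353.

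n = [1.645·√(2·0.353·0.647) + 0.842·√(0.203·0.797 + 0.503·0.497)]² / 0.30²

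= (1.112 + 0.540)² / 0.09 = 30.3, rounded up to 31 per arm.

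With 9 of 40 lost, 31 / (1 − 0.225) = 40. Both stated figures reproduce, and the point does not change the sample size.

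**3. Effect of selective removal (illustration).** Assumption: 40 randomized per arm, and k failures removed from one arm only. The protocol gives no expected number of such events, so k is chosen for illustration.

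With both true rates at 20.3%, the expected number of successes is 40 × 0.203 = 8.12 per arm. The affected arm's expected rate becomes 8.12 / (40 − k). The type I error is found by summing the binomial probabilities of all tables in which the one-sided test rejects at 0.05 after the k failures have been deleted.

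| Failures removed | Rate in affected arm | Spurious difference (clindamycin minus placebo) | Type I error, chi-squared (uncorrected) | Type I error, Fisher |
|---|---|---|---|---|
| none | 20.3% | 0 | 5.1% | 3.0% |
| 2, clindamycin | 21.4% | +1.1 points | 6.5% | 3.8% |
| 4, clindamycin | 22.6% | +2.3 points | 8.2% | 5.0% |
| 4, placebo | 22.6% | −2.3 points | 3.2% | 1.6% |

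Removing 9 clindamycin failures, the whole loss allowance for that arm, would give a Fisher type I error of 10.5%; this is an upper illustration only.

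At the design rates, the expected clindamycin successes are 40 × 0.503 = 20.12. Removing 4 clindamycin failures turns the 30-point difference into 20.12/36 − 0.203 = 35.6 points. Removing 4 placebo failures turns it into 0.503 − 8.12/36 = 27.7 points.

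**The case against.** The strongest reply is that the text does less than it seems to. A reader might infer that outcomes already collected as routine care are thrown away, but no sentence says so. The stated aim is to include everyone randomized, and the limit to results already held applies to participants who withdraw, not to those whose participation is ended for them. That stands, and it is why the loss is described here as probable.

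The Concomitant care rule can also be read narrowly, so that admission matters only if it interferes with taking capsules over the 10 days. On that reading, infections after the course fall under the exclusion wording alone, and no section describes actually removing someone who later receives antibiotics. This reading is possible, and the uncertainty is itself a reason to clarify.

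A reader might think that serious events disappear from view. They do not: Harms {22} follows adverse events until they resolve or observation is no longer medically indicated, and serious events are reported to the authorities. The issue concerns efficacy outcomes.

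A reader might also conclude that one participant could decide the trial. With 6/31 against 12/31, one-sided chi-squared p = 0.047; adding back one clindamycin failure (12/32) gives 0.055. This pair sits at the threshold by choice. Fisher's test is non-significant both ways (0.080 and 0.094). Near the design rates, 6/31 against 16/31 gives a chi-squared p of 0.004, and adding back four clindamycin failures (16/35) still gives 0.012.

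Finally, recovering the result may take some effort. The laboratory route, "we automatically obtain information about all MRSA culture-positive samples in the lab on daily basis", covers positive cultures only, and the protocol does not say that GP swabbing is unchanged for someone who leaves mid-course. This too stands: the loss is often avoidable, but not automatically.

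**Conclusion.** The point holds in a limited form. The written rules end participation, and list an exclusion, on events after randomization, without saying that outcome follow-up continues. With the omission and complete-case rules, this probably removes participants from the primary analysis, against the plan's own intention.

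The links to arm and outcome are inferences from the protocol's text, not measured quantities. The direction of bias is open, and its size cannot be derived because no event count is given; it is likely small if events are few. The illustrated rise in type I error from 5.1% to 8.2% (chi-squared) or from 3.0% to 5.0% (Fisher) rests on the assumption that four participants are removed, all of them clindamycin failures.

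The change is worth making because it is cheap and protects the randomized comparison. How outside MRSA-active antibiotics enter the primary analysis is a choice of estimand, and the protocol does not settle it.

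**What to change.** - State that ending study treatment does not end outcome follow-up. Unless consent is withdrawn, obtain the routine 1-month GP swab, and the 6–8-month swab if the first is negative, and analyse the participant as randomized.
- Reword the antibiotic eligibility criterion so that it covers only what is known before randomization.
- Record later MRSA-active antibiotics as an intercurrent event and pre-specify their handling in the primary analysis. Report the result both with the swab as observed and with these participants counted as failures. The second version is needed because an uncleared carrier who is treated for an infection and then swabs negative would otherwise count as a success.

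None of this alters when study treatment is stopped or how participants are treated. The cost is a short amendment, a little extra follow-up and one additional analysis. The downside is some dilution of the comparison by outside antibiotics, which reporting both versions makes visible.

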### Disadvantages, advantages, risks, and adverse events

The disadvantages include antibiotic consumption by healthy individuals. It is well-known that antibiotic consumption changes the microbiome of the intestine for a longer period, but the impact of this influence is still rather unknown. Furthermore, antibiotic consumption leads to selection for antibiotic resistance. According to the investigational product information, less than 10% of clindamycin consumers will experience side effects, most commonly of gastrointestinal characters such as abdominal pain and diarrhea. Skin rash is also a common side effect seen in 1 to 10%.

Advantages for the participant receiving clindamycin include the possibility of becoming MRSA-free at an earlier time point, than had the carrier not participated in the trial.

The greatest advantage is gathering evidence to optimize the treatment of future MRSA carriers.

The results from this study will impact the future recommendations for decolonization regimens.

### Harms {22}

An adverse event (AE) is any untoward medical occurrence in a study subject administered a test product, whether considered related to the study treatment or not.

AEs recorded in the diary, including onset, end, intensity, causality, action taken, and outcome of the AE, will be reported in the eCRF (REDCap). Participants will be followed up by the medical judgment of the investigator, until the abnormal condition is resolved or the investigator deems further observations or examinations to be no longer medically indicated.

Causality is evaluated by the investigator and sponsor. In case of incongruency, both evaluations will be reported.

#### Serious adverse events

A serious adverse event (SAE) is any untoward medical occurrence that, at any dose, is life-threatening at the time of the event, requires hospitalization or prolongation of existing hospitalization, results in persistent or significant disability or incapacity, is another important medical event, results in congenital anomaly or birth defect, or results in death. If an SAE occurs, the SAE will be reported to the authorities and will be handled in accordance with local regulations.

Known adverse reactions of clindamycin may be experienced in approximately 0.1–10% according to the clindamycin product information, most commonly:Gastrointestinal: abdominal pain, pseudomembranous colitis, nausea, vomiting, and diarrheaHypersensitivity reactions: generalized mild to moderate morbilliform-like (maculopapular) skin rashLiver: jaundice and abnormalities in liver function tests have been observed during clindamycin therapy

### Statistics {20a/b/c}

Continuous data are expressed as median and range. Power calculations are based on an expected proportion of 20.3% in the control group and a minimum relevant difference of 30% points resulting in an expected 50.3% in the intervention group. Power is set at 80 and significance level at 0.05%. Since only superiority is of interest, a one-tailed *p*-value will be used. The statistical software “R” [17] was used for power calculation. The analysis will be performed using Fisher’s exact test or chi-squared test depending on sample size. Statistical calculations will be performed using IBM SPSS Statistics, version 25, IBM Corporation, and other(s) 1989, 2018. We intend to include every study participant randomized in the primary analysis, only omitting excluded participants, where no data is available after randomization or in case of lack of compliance. Missing data will be excluded from the analysis. No subgroup or interim {21b} analysis is planned.

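### The printed significance level of 0.05% contradicts the 31 per group, which follows from one-sided 5%; most likely a misprint to correct, with no change of design

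*Protocol article*

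**What the plan says.** The Statistics section of the protocol article holds the inputs to the power calculation. It says that "Power calculations are based on an expected proportion of 20.3% in the control group" and on "a minimum relevant difference of 30% points resulting in an expected 50.3% in the intervention group". It then says "Power is set at 80 and significance level at 0.05", where a percent sign follows 0.05 but none follows 80. The next sentence fixes the direction of the test: "Since only superiority is of interest, a one-tailed *p*-value will be used". The test itself is left between two options: "The analysis will be performed using Fisher’s exact test or chi-squared test depending on sample size".

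The result of the calculation stands in the Sample size section: "Power calculation shows that we will need 31 patients in each group". The recruitment target is built on it: "It is our goal to include 40 patients in each group, as we expect that 9 patients in each group will either drop out" or not comply with treatment (31 + 9 = 40).

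No other section of the article gives a significance level.

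**The concern.** A level of 0.05% is a probability of 0.0005, one hundredth of the usual 0.05. A calculation at that level with these rates could not have produced 31 per group, so the printed level and the printed sample size cannot both be right.

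Because the level appears only once, nothing else in the article corrects it, and a reader would naturally carry it over to the final test. A p-value between 0.0005 and 0.05 would count as success on one reading and not on the other. Nor is the intended level plain at sight: someone who spots the slip still has to recalculate to learn that 31 belongs to a one-sided 5% level and not to a two-sided 5% level.

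**Working it through.** **Inputs.** From the Statistics section: p1 = 0.203, p2 = 0.503, difference d = 0.300, power 80% (printed as 80), one-sided test, alpha printed as 0.05%. From the Sample size section: 31 per group needed, 40 per group planned, equal groups.

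**Formula (pooled normal approximation, no continuity correction).**

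n per group = [z(1−alpha) × √(2 p̄ q̄) + z(power) × √(p1 q1 + p2 q2)]² / d²

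- p̄ = (0.203 + 0.503)/2 = 0.353 and q̄ = 0.647, so √(2 × 0.353 × 0.647) = √0.45678 = 0.6759.
- √(0.203 × 0.797 + 0.503 × 0.497) = √0.41178 = 0.6417.
- z(0.80) = 0.8416.

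**Step 1: reproduce the 31, with one-sided alpha = 0.05 (z = 1.6449).**

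n = (1.6449 × 0.6759 + 0.8416 × 0.6417)² / 0.09 = (1.1117 + 0.5401)² / 0.09 = 30.3, so 31. This matches the article.

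Power at 31 = Φ[(0.3 × √31 − 1.1117) / 0.6417] = Φ(0.871) = 80.8%.

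**Step 2: the level as printed, one-sided alpha = 0.0005 (z = 3.2905).**

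n = (3.2905 × 0.6759 + 0.5401)² / 0.09 = (2.2239 + 0.5401)² / 0.09 = 84.9, so 85.

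Power at 31 = Φ[(0.3 × √31 − 2.2239) / 0.6417] = Φ(−0.863) = 19.4%.

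Power at 40 = Φ[(0.3 × √40 − 2.2239) / 0.6417] = Φ(−0.509) = 30.5%.

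**Step 3: power by the two tests that the article names**, by exact enumeration of all outcomes.

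| One-sided alpha | Per group | Pooled normal | Chi-squared, exact | Fisher's exact |
|---|---|---|---|---|
| 0.05 | 31 | 80.8% | 80.5% | 72.8% |
| 0.05 | 40 | 89.0% | 89.2% | 83.5% |
| 0.0005 | 31 | 19.4% | 19.9% | 13.7% |
| 0.0005 | 40 | 30.5% | 30.7% | 24.9% |

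**Step 4: could another method reconcile 0.05% with 31?** At one-sided 0.0005, the unpooled formula gives 79 per group, the arcsine formula 83 and the continuity-corrected formula 92. None is near 31. The unpooled and arcsine approximations put power at 31 at 24.6% and 22.3%, still far below 80%.

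**Step 5: which level does 31 imply?** At one-sided 0.05 the other formulas give 29 (unpooled), 30 (arcsine) and 37 (continuity-corrected); the pooled formula gives exactly 31. At two-sided 0.05 the pooled formula gives 39. Solving the pooled formula for the alpha that gives 80% power at 31 yields 0.047 one-sided, which fits 0.05 after rounding n up.

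**The case against.** The strongest reply is that this is a misplaced percent sign. The same sentence leaves the sign off 80 and puts one after 0.05. The article publishes both rates, the power, the sidedness and n, and together they identify alpha = 0.05. That reply stands as to what was meant, and it limits the harm. It does not remove the need to correct the figure.

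A reader might infer more than the document supports, in four ways.

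- *That the trial has about 19% power.* That would be the power of a trial analysed at the misprint. The trial as sized has about 80% power with the chi-squared test.
- *That 0.05% is the stated threshold for declaring success.* The figure stands among the sentences on the power calculation, and the article gives no separate level for the final test. Carrying it over is natural but remains an inference; the analysis plan, which may exist, is not at hand.
- *That a later correction would destroy pre-specification.* The published inputs already tie the intended level to one-sided 5%, so a move to any other level would be visible. An early correction is tidier, but the stronger claim goes too far.
- *That the one-tailed test is itself an error, or must be restated as two-sided 10%.* The article declares the choice and gives its reason. Restating it is a reporting preference.

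One qualification runs the other way. The 80% is not assured under both named tests: with Fisher's exact test, power at one-sided 5% is about 73% at 31 per group, and reaches about 84% only if all 40 per group are analysed.

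**Conclusion.** The contradiction is real and does not depend on the method of calculation: the printed level is one hundredth of the level that yields 31 per group. Taken literally, it would require about 85 per group instead of 31, and power would be about 14% to 20% at 31 and 25% to 31% at 40, according to the test.

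It is most likely a misprint for 0.05, so this is an error in a stated figure and not a failure of design. That judgement rests on reading 80 as 80%, on the pooled normal approximation without continuity correction, on the article's own rates, and on 31 analysed per group. Under those assumptions the sample size is right at one-sided 5% with the chi-squared test. The correction is minor in effort and consequence, but it concerns the only significance level that the article gives.

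**What to change.** Before the investigators are unblinded at the end of the trial, correct the sentence in the Statistics section, with a date, to read: *power is set at 80% and the one-sided significance level at 5% (alpha = 0.05)*. Naming the side together with the level prevents a reading as two-sided 5%. If the full protocol or the analysis plan repeats the figure, correct it there too.

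The cost is one corrected sentence. Sample size, recruitment target and conduct do not change. A two-sided 95% confidence interval for the difference may be reported as well, but that is optional and not part of the error.

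### The primary analysis is announced as all-randomised, but its own exclusions make it a per-protocol, complete-case comparison that risks selection bias

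*Protocol article*

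**What the plan says.** All references are to the protocol article.

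- **Statistics {20a/b/c}**, intention: "We intend to include every study participant randomized in the primary analysis".
- **Same sentence**, exceptions: "only omitting excluded participants, where no data is available after randomization or in case of lack of compliance". The next sentence adds: "Missing data will be excluded from the analysis".
- **Compliance and adherence {11c}** supplies the threshold: "Compliance is defined by having consumed more than 80% of the oral capsules". It also states: "We expect patients in both groups to be equally compliant".
- **Sample size {14}** gives 31 per group from the power calculation and raises it to 40, "as we expect that 9 patients in each group will either drop out or be non-compliant to the treatment".
- **Concomitant care {11d}**: "Hospitalization and other interventions interfering with the compliance of the trial will inevitably result in terminated trial participation".
- **Modifications {11b}** allows results already held at withdrawal to be used.

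No other section names a different primary analysis set.

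**The concern.** The intention and the exceptions cannot both hold. Whichever way the exception clause is parsed, a participant who took 80% or fewer of the capsules leaves the primary analysis, and so does anyone without a swab result. What remains is the compliant participants with data, not the randomised groups.

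Capsule-taking is observed after randomisation and can be affected by the capsules. The section on disadvantages and risks says that "less than 10% of clindamycin consumers will experience side effects, most commonly of gastrointestinal characters such as abdominal pain and diarrhea", and both it and the section on serious adverse events list rash. Such effects could stop participants taking the capsules more often on clindamycin than on placebo. If those who stop also differ in their chance of clearing MRSA, the remaining groups differ for reasons other than the drug's effect on carriage.

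The estimand is also at stake. The Discussion asks whether clindamycin should have a place in decolonisation and whether its benefit justifies its side effects. That decision needs the effect of being allocated clindamycin, including in people who cannot finish it. The rule also discards outcomes that may exist: the 1-month swab is a routine general-practice sample and does not depend on finishing the capsules.

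**Working it through.** **1. The plan's own figure.** Inputs from the Statistics section: 20.3% v 50.3%, one-sided test, 80% power. The significance level is taken as 5%; it is printed as 0.05%, which is a separate point. Pooled-variance normal formula, mean rate (0.203 + 0.503)/2 = 0.353:

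n = [1.645·√(2·0.353·0.647) + 0.842·√(0.203·0.797 + 0.503·0.497)]² / 0.30² = 30.3, rounded up to **31 per arm**.

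This matches the plan. Inflation: 31/(1 − 9/40) = 40, which also matches. The powered set is therefore the 31 compliant participants with data, and 9/40 = 22.5% per arm are expected to fall outside it.

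**2. What exclusion can do when there is no true effect.** Assume 20.3% success among all 40 in each arm. If a fraction c of an arm is non-compliant and those participants clear at rate r, the retained success rate is (0.203 − c·r)/(1 − c). The values of c and r are assumptions; the protocol gives none by arm.

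| Non-compliance, clindamycin v placebo | r | Retained rates | Spurious difference | One-sided rejection, normal | One-sided rejection, Fisher |
|---|---|---|---|---|---|
| 22.5% v 22.5% | same in both arms | equal | 0 | 5.0% | 2.4% (at r = 20.3%) |
| 27.5% v 17.5% | 10% | 24.2% v 22.5% | +1.7 points | 6.9% | 3.9% |
| 27.5% v 17.5% | 0 | 28.0% v 24.6% | +3.4 points | 9.0% | 5.6% |
| 30% v 15% | 0 | 29.0% v 23.9% | +5.1 points | about 12% | 6.7% |

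Example, row 3: 0.203/0.725 = 0.280 and 0.203/0.825 = 0.246. Retained numbers are 29 v 33 in rows 2 and 3, and 28 v 34 in row 4. Fisher rates come from exact enumeration; the test is conservative, so its reference with no selection is 2.4% at 31 per arm, not 5%. Swapping the non-compliance figures between arms reverses the sign of each difference.

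**3. Power if all 40 per arm are analysed as allocated.** Two assumptions about the 9 per arm:

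- They clear at the control rate. Clindamycin: (31·0.503 + 9·0.203)/40 = 43.6%; control 20.3%.
- They count as failures. Clindamycin: 31·0.503/40 = 39.0%; control: 31·0.203/40 = 15.7%.

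The difference is 23.3 points in both cases.

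| Set | Normal approximation | One-sided Fisher |
|---|---|---|
| Plan: 31 v 31, 20.3% v 50.3% | 81% | 73% |
| 40 v 40, the 9 clear at control rate | 73% | 65% |
| 40 v 40, the 9 count as failures | 76% | 69% |

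Within one test the fall is about 4–8 points. Restoring 80% by the normal formula would take 49 or 45 per arm respectively.

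**The case against.** The strongest reply is that the risk is small. The trial is double-blind with identical capsules, and the protocol expects equal compliance. Side effects are put at under 10% of clindamycin users, and not all of those would stop, so a 15-point excess of non-compliance goes beyond the document's own figure. With no true effect, missing capsules would not in itself prevent clearance. A link with outcome needs a further assumption, such as poor adherence to the topical treatment as well. The 9 per arm also pools dropout with non-compliance, so missing swabs may be fewer, and reminders are sent for unregistered swabs.

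Most of this stands as a limit on size. It does not restore the all-randomised set: blinding does not prevent stopping caused by the drug, and equal compliance is an expectation rather than a safeguard.

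A reader might infer three stronger things that the documents do not support:

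- **The analysis will favour clindamycin.** Nothing in the protocol fixes the direction.
- **Type I error is 12%.** That is the severest scenario shown, under one test only; Fisher gives 6.7%.
- **Correcting the rule cuts power from 80% to 65%.** That compares the formula-based figure with a Fisher figure. Fisher gives only 73% at the plan's own 31 per arm, so part of that gap comes from the choice of test.

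An unseen analysis plan does not answer the point, because the exclusion is a stated rule on which the sample size rests.

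**Conclusion.** The point holds as a contradiction in a stated rule: the primary comparison is per-protocol and complete-case although announced as all-randomised. The resulting selection bias is possible, not demonstrated. On assumed inputs under no true effect it ranges from nil to about 5 points, with one-sided rejection up to about 12% (normal; reference 5%) or 6.7% (Fisher; reference 2.4%). The upper end needs both a 15-point gap in non-compliance and no clearance among non-compliers. The sample size of 31 is not an arithmetic error; it reproduces, but for the compliant set only. The matter deserves correction because it governs the single primary comparison, with up to 22.5% per arm expected to be left out.

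**What to change.** Replace the sentence on the analysis set with wording such as: *The primary analysis includes all randomised participants in their allocated arm, regardless of capsules taken, using every available 1-month swab.*

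Then:

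- Prespecify a rule for a missing 1-month swab. Counting it as not decolonised is one option; it can itself bias the result if missingness differs by arm, so add complete-case and best/worst-case sensitivity analyses.
- Move the set with more than 80% of capsules taken to a supportive per-protocol analysis.
- Reconcile Modifications {11b} and Concomitant care {11d} with the analysis set, so that the 1-month swab is still used, where consent allows, after capsules are stopped or participation ends. Otherwise many outcomes would be imputed rather than observed.
- Restate power for 40 per arm within one named test, with the assumption made about the 9 per arm.

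The cost is wording, some attention to follow-up data, and a stated power 4–8 points lower. No extra patients are needed if that is accepted; keeping 80% by the normal formula would need 45–49 per arm. The change should be settled before the data are unblinded for analysis.
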